##### Incremental health gain in quality (CYP and parents)

Quality-adjusted life years (QALYs) will be estimated using the Child Health Utility 9D (CHU-9D). To inform a future economic evaluation, we shall use the CHU-9D [26], which has been validated for CYP aged 7–17 to estimate incremental health gain in QALYs. It uses a descriptive system and a set of preference weights. Utility values are assigned to each health state that is described by the descriptive system, which can be calculated on the basis of QALYs for use in cost utility analysis. The descriptive system consists of nine dimensions, namely Worried, Sad, Pain, Tired, Annoyed, Schoolwork/Homework, Sleep, Daily Routine, and Activities. Each dimension has five levels. The measure is preference-based and therefore suitable for use in paediatric economic evaluation.

##### Symptoms of common mental health problems (CYP and parents)

Symptoms of common mental health problems will be captured using the Revised Child Anxiety and Depression Scale [27], which is a 47-item questionnaire that measures the reported frequency of anxiety and low mood. The measure has been validated for CYP aged 8–18. A parent report is also available. It measures a total score for anxiety and low mood, corresponding to the DSM diagnoses of separation anxiety, social phobia, generalised anxiety, panic, obsessive compulsive, and major depressive disorder. Each item uses a 4-point scale and is assigned with a 0–3 numerical value, with responses as ‘never’ (0 points), ‘sometimes’ (1 point), ‘often’ (2 points) and ‘always’ (3 points). Scores are calculated by converting the raw scores into the corresponding T-scores. While a T-score of 65 or higher indicates the borderline clinical threshold, a T-score of 70 or higher indicates above the clinical threshold for anxiety and depression.

##### Children’s knowledge and perceptions about SMI (mental health literacy) (CYP only)

We shall use the Mental Health Literacy Questionnaire [28, 29] to assess the CYP’s knowledge and perceptions about SMI (mental health literacy) and their problem-solving skills. The measure has 48-items and is divided into four sections as (1) sociodemographic information; (2) knowledge about mental health problems (32-items); (3) first aid skills and help seeking (10-items); and (4) self-help strategies (6-items). Each item has a 5-point Likert scale, ranging from ‘strongly disagree’ (1 point) to ‘strongly agree’ (5 points). The last item has a multiple-choice option, asking CYP to identify mental health problems from a list of 11 health problems. Higher scores indicate higher levels of mental health literacy.

##### Parenting competencies (parents only)

We shall measure parenting skills and child-parent relationships using the Arnold-O’Leary parenting scale [30]. This tool is a 30-item questionnaire that measures parents on three factors, namely Laxness (11 items), Over-Reactivity (10 items) and Verbosity (7 items). Four more items are not on a factor. Each item has a 7-point Likert scale (7 being the ‘ineffective’ end of the item). Total scores are calculated as an average of the responses on all items. Factor scores are calculated as an average of the responses on the items in that factor. Higher scores indicate higher degrees of parental laxness, over-reactivity and verbosity.

##### The degree and cause of stress in a parent–child relationship (parents only)

The degree and cause of stress in a parent–child relationship was measured using the Parenting Stress Index/Short Form [31]. This tool has 36-items that are divided into three categories of stress, namely Parental Distress, Parent-Child Dysfunctional Interaction and Difficult Child, which combine to form a Total Stress scale. Scores are calculated by converting raw scores into percentile and T-scores. To be in the ‘normal range’ of parental stress, parents have to be in between 16th to 84th percentile; to be in the ‘high range’, parents have to be in between the 85th to 89th percentile; and to be in the ‘clinically significant range’, parents had to be in the 90th percentile or above. A Defensive Responding score is clinically significant when the raw score is 10 or lower.

### Resource use

Resource use will be assessed using the Child & Adolescent Service Use Schedule designed in previous research [32], adapted for the purpose of the current trial. It will collect information on receipt of care and services by each family in relation to CYP needs and services from the NHS, social care, education, voluntary and third sector organisations. The cost of this resource use will be primarily calculated from the NHS and Personal Social Services perspective, with a secondary wider societal perspective estimate also calculated in light of the societal/community context of the intervention.

### Acceptability

The success of intervention implementation heavily relies on its acceptance by those in receipt of and those delivering an intervention. A qualitative evaluation of the intervention will be conducted via interviews or focus groups with CYP, parents/carers and practitioners post intervention, at 3 months. All individuals who accessed or delivered Young SMILES will be invited to participate, including those who leave treatment early. All individuals who express an interest in taking part will be given the option of taking part in an individual interview or focus group. If participation in a focus group is selected, in order to ensure participants feel at ease, group composition will be considered and the different stakeholders (CYP of differing age bands, parents and professionals) will take part in separate group discussions.

Semi-structured interview schedules will be prepared to guide the discussions. Interviews with CYP and parents/carers will focus on identifying barriers and facilitators to attending, what they liked and disliked, and if they think Young SMILES has helped their family. Discussions with children will follow the semi-structured interview schedule but will additionally use child-centred approaches such as drawing or inclusion of visual resources to aid understanding and enhance data collection. Practitioner interviews will perceptively explore what factors may facilitate or hinder the implementation of Young SMILES.

At baseline, we will additionally ask the parent or carer and the child to complete a demographic questionnaire.

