**Methods/design:**

An age-appropriate standardised intervention for COPMI, called Young SMILES, was developed in collaboration with service users, National Health Service (NHS) and non-NHS stakeholders in our previous work. This protocol describes a randomised feasibility trial comparing Young SMILES with usual care, involving 60 families that will be identified through third sector organisations and NHS services, and recruited and randomised on a 1:1 basis to receive Young SMILES or usual care. Outcomes of the feasibility trial are rates of recruitment, follow-up and withdrawals, intervention uptake, and engagement. The optimal child-reported outcomes will also be determined alongside the assessment of resource use. A qualitative evaluation conducted at 3-months will explore the experiences and views of children and young people as well as parents accessing the intervention and the facilitators delivering the intervention.

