### Blinding

Randomisation will be conducted by the study co-ordinator to maintain blinding of the statistician and research team to reduce detection bias. To facilitate blinding, we will (1) ensure that families know that they can contact the study coordinator should they have any queries about their allocation or the Young SMILES intervention arrangements and (2) the researcher conducting the data collection visits will remind families to refrain from revealing their allocation to them during follow-up visits. Should a researcher become aware of any allocations, this will be recorded and reported.

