### Protocol changes

Since the trial commenced, a number of protocol changes have been made. These are detailed in Table 4. Applications to the Research Ethics Committee (REC)/HRA have been made and approved for all changes outlined.

**Table 4 Tab4:** Protocol changes made since the trial commenced

Aspect of trial	Changes made
Primary outcome point	Change from 3-months to 4-months. Due to family availability and referral rates, baseline interviews have been conducted over a longer time period than was anticipated. As a result, some families were being offered a 3-month follow-up appointment while still accessing the Young SMILES intervention (if randomised to that trial arm). To ensure the amount of ‘useful data’ is maximised, the primary outcome point was changed to 4 months, without altering the 6- and 12-month time points
Data collection	Addition of demographic questionnaire for all participants taking part in the feasibility trial (children and young people, parents, carers) Addition of referrer interviews to explore the experiences of individuals who have referred to the study and also those who have been approached but have not referred any families; individuals will be from health, social care, educational and third sector services, which will aid a more thorough understanding of the development of referral pathways that will add to the other findings from the feasibility study to assist with the development of an application for a full-scale trial
Randomisation	Change from using the Sealed Envelope system (www.sealedenvelope.com) to randomise 60 families on a 1:1 ratio either to Young SMILES or to usual care to online randomisation software (www.randomization.com), which would better meet study requirements in relation to sample size and the ability to stratify by age and site, without incurring costs Addition of 2:1 randomisation allocation procedures (2 Young SMILES intervention; 1 control) to expedite start of intervention groups; this has been acknowledged to be wholly appropriate for a feasibility trial in such a ‘specified group’ intervention
Intervention delivery	Inclusion of siblings within the same group (if in the same age band) Submission of young person travel consent form for parents/carers to consent to child/adolescent travelling to the intervention venue alone

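### No rule places the Young SMILES-only interviews after the primary outcome booklet, and their 3-month timing was not restated when the primary outcome point moved to 4 months

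*Protocol article*

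**What the plan says.** The Acceptability section sets both who is interviewed and when: "A qualitative evaluation of the intervention will be conducted via interviews or focus groups with CYP, parents/carers and practitioners post intervention, at 3 months". The Abstract gives the same time: "A qualitative evaluation conducted at 3-months will explore the experiences and views of children and young people". The invitation covers one arm and the staff who deliver the programme: "All individuals who accessed or delivered Young SMILES will be invited to participate, including those who leave treatment early". Topics for children and parents include "what they liked and disliked, and if they think Young SMILES has helped their family".

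Table 4 records the approved change: "the primary outcome point was changed to 4 months, without altering the 6- and 12-month time points". Its reason is that "some families were being offered a 3-month follow-up appointment while still accessing the Young SMILES intervention".

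The primary outcome is the child's health-related quality of life, measured by the Pediatric Quality of Life Inventory and KIDSCREEN. The measures are designed for self-completion, and researchers may help (Outcome assessment; Recruitment). On masking, the Blinding section states: "Randomisation will be conducted by the study co-ordinator to maintain blinding of the statistician and research team to reduce detection bias". It adds that families are reminded at data collection visits not to disclose their arm, and that any unblinding is recorded and reported.

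**The concern.** The interviews are a structured conversation about whether the programme worked, held with one arm only. If that conversation comes before the outcome booklet, intervention families answer the primary measures after being prompted to think about benefit, and control families do not. The Intervention effectiveness section says that the estimated effect and variability will be used to design the definitive trial, so an avoidable difference between arms in how the outcome is collected matters even in a feasibility study.

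There are two related points. First, for families who had not finished the programme at 3 months, the Acceptability section asks for something impossible. Second, whoever interviews a family about Young SMILES learns that family's arm, and the article does not say whether that person also visits families to collect outcomes.

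**Working it through.** No sample size, power or error rate depends on this point. The check sets the sections side by side and does date arithmetic.

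**Inputs from the article**
- Programme length: 8 weeks (Intervention – Young SMILES).
- Follow-up counted from the baseline assessment (Trial design).
- Primary outcome point: 4 months, previously 3 (Table 4).
- Interviews: after the intervention, at 3 months (Abstract; Acceptability).
- First group in January 2018, interviews from March 2018 (Forecast execution dates).

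**Assumptions.** One month is 30.44 days. The wait from baseline to the first session is not given, so 0 to 10 weeks is used. Eight weekly sessions span 7 weeks from first to last, or 8 weeks if the final week is counted in full.

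**Step 1: can an interview be both after the programme and at 3 months?**
Longest wait that allows this = follow-up point in weeks − programme span.
- 3 months = 3 × 30.44 / 7 = 13.0 weeks. Longest wait = 13.0 − 8 = 5.0 weeks, or 13.0 − 7 = 6.0 weeks.
- 4 months = 4 × 30.44 / 7 = 17.4 weeks. Longest wait = 17.4 − 8 = 9.4 weeks, or 17.4 − 7 = 10.4 weeks.

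A family that waits more than about 5 to 6 weeks is still in the programme at 3 months. Table 4 confirms that such families exist. For them the two conditions on the interview conflict.

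**Step 2: which comes first, interview or primary outcome?**
Read literally, the interview precedes the outcome by 4 − 3 = 1 month. The calendar shows that the order in practice depends on the wait. For a group starting on 15 January 2018, with its last session on 5 March:

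| Wait | Baseline | 3 months | 4 months |
|---|---|---|---|
| 2 weeks | 1 January | 2 April | 3 May |
| 8 weeks | 20 November 2017 | 19 February | 22 March |

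In the first row a 3-month interview falls after the programme and a month before the primary outcome. In the second row the 3-month point falls before the last session. An interview held after the programme could then come on either side of 22 March.

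Across January start dates from the 2nd to the 31st, the 4-month point falls between 6 April and 2 June for waits of 0 to 4 weeks. Interviews from March can precede it. For waits of 8 to 10 weeks it falls between 23 February and 7 April, before or around the interview.

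**Step 3: does any other section settle the order?**
- Table 4 reopens the qualitative work by adding referrer interviews, but gives no new time for the family interviews.
- The Qualitative analysis section keeps the qualitative analysts unaware of trial outcomes. It does not protect outcome collection from the interviews.
- The Blinding section deals with data collection visits and does not mention the interviews.
- No section says whether the booklet or the interview comes first, or who conducts the interviews.

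**The case against.** The strongest reply is that the body text was not updated for other amendments either. Trial design still has the 3-month visit, Randomisation still has only 1:1 allocation, and Recruitment still separates siblings in the same age band. The interview's 3 months matches the old follow-up point and may have moved with the visit. A difference between a change table and unamended text is not in itself an error. This stands as far as it goes: a deliberate decision to hold interviews a month before the primary outcome cannot be read from the article. It does not supply the missing rule. If the interviews did move to 4 months, the order within that visit is still open, as it was when both were at 3 months.

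A reader might also infer that the interviews undo the research team's blinding for all later visits. The article does not support that. It never says that interviewers collect outcomes, the study co-ordinator who performs the randomisation already handles allocation queries, and staffing detail is commonly left to the full protocol.

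A further objection is that families know their arm in any case, and that the last child and parent sessions already review progress and achievements. The interview therefore adds to reflection that the programme itself prompts. This is fair, and it limits how much bias the interview could add.

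**Conclusion.** The concern holds as a gap in sequencing. Followed as written, the plan allows one arm to be asked about benefit before completing the self-reported primary outcome, and it sets an interview time that some families cannot meet. It rests on a literal reading of Acceptability beside Table 4 and on the absence of any ordering rule. The actual order will differ between families.

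The size of any bias cannot be derived. The article gives neither an interview effect nor a target effect, and interview uptake is unknown because only those who express an interest take part. A figure in standard deviation units would have no source. The bias is probably modest. That the interviewer learns allocation is certain; that outcome assessment is thereby unblinded is only possible.

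A reader might go on to conclude that follow-up should be counted from the start of each group. That is a separate question about visit timing, would disturb the 6- and 12-month points that Table 4 leaves alone, and is not needed here.

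**What to change.** 1. Reconcile the Abstract, Trial design and Acceptability with Table 4, so that interview time and primary outcome time are stated once and agree.
2. State that each family's interview or focus group takes place only after its 4-month outcome booklet is complete, either later in the same visit or afterwards.
3. Where existing staffing allows, a researcher who has interviewed a family should not collect its later outcomes. Otherwise, record that researcher as unblinded for the family under the existing rule in the Blinding section.

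The cost is a few sentences and a shift of about a month in the interviews, with slightly longer recall. Separating interviewers from assessors could add staffing and travel, and the article already reports pressure on the travel budget, so item 3 is conditional. Interviews were due from March 2018 and recruitment is in its final stages, so the ordering rule can only help families not yet interviewed.

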### Sample size

The proposed sample size of 60 randomised families (30 per group as recommended for pilot studies [33]) is adequate to facilitate the main aims of the study such as establishing feasibility and informing a future power calculation. Formal power calculations are not appropriate for this feasibility study.

We aim to run a minimum of three sets of child and adolescent groups and three parallel parent groups over the three recruitment sites during the recruitment period. We shall offer the parenting element of the intervention to both the ‘ill’ and the ‘well’ parent /carer (if they both wish to participate) or a significant family member, and we shall offer child- and adolescent-centred work to all eligible CYP within each family.

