#### Intervention – Young SMILES

Young SMILES is a service for CYP (aged 6–16) whose parents live with SMI, aiming specifically to improve the HRQoL of CYP. The intervention was co-developed in the earlier phase of this research via consultation with stakeholders (CYP of parents with serious mental illness, parents and practitioners from third sectors and NHS organisations). Young SMILES is an 8-week group programme (4–6 CYP per group) split into two age bands, namely 6–11 and 12–16. At week 4, five parallel sessions are offered to the parent or significant other adult. CYP and parent sessions last for 2 hours, which includes time for a short break and refreshments during and after the group. Where possible, the sessions will be held in a non-stigmatising venue such as a community location rather than a hospital clinic or school.

Sessions will be facilitated by two trained practitioners. The expertise and skills of the facilitators is an invaluable aspect of the Young SMILES intervention. Groups will be delivered in an NHS organisation using a co-delivery model where one facilitator is from the NHS (family therapy background) and the other is from a third sector organisation. Third sector organisation facilitators will have a variety of professional backgrounds such as social workers, children’s service practitioners, psychologists and occupational therapists.

Intervention facilitators will be provided with a 3-day training session. A training manual for facilitators was developed as part of the development phase which provides an overview of the feasibility trial and development of Young SMILES. It additionally incorporates structured detail on service delivery and intervention delivery, providing an on-going guide/reference for practitioners who deliver the service and manual to support trainers to ‘teach’ practitioners the aspects of the model and how it should be delivered.

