### Randomisation

Following agreement to participate via written consent and completion of baseline outcome measures, families will be randomised on a 1:1 ratio either to Young SMILES or to usual care using a central, independent, free web-based system [34].

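### The sample-size paragraph still justifies 60 families by 30 per group, but with the approved 2:1 allocation 60 families cannot be expected to give 30 controls

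*Protocol article*

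**What the plan says.** The Sample size section of the protocol article makes one adequacy statement: "The proposed sample size of 60 randomised families (30 per group as recommended for pilot studies [33]) is adequate to facilitate the main aims". The aims it names are establishing feasibility and informing a later power calculation. It adds that "Formal power calculations are not appropriate for this feasibility study", so the per-group figure is the whole justification.

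The Randomisation section matches that figure: "families will be randomised on a 1:1 ratio either to Young SMILES or to usual care". The abstract also gives 1:1.

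Table 4 in the Protocol changes section then lists, among changes made after the trial began: "Addition of 2:1 randomisation allocation procedures (2 Young SMILES intervention; 1 control) to expedite start of intervention groups". The text introducing the table says: "Applications to the Research Ethics Committee (REC)/HRA have been made and approved for all changes outlined". Neither the table nor any other section says from which family 2:1 applies, whether the total of 60 changes, or what arm sizes are now expected.

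**The concern.** A total of 60 gives 30 per group only under equal allocation. Once some families are allocated 2:1 and the total stays at 60, the expected control arm is below 30. The one figure on which the article rests its adequacy statement is then not delivered for that arm.

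This affects what the trial is meant to hand on. The Statistical analysis section reports follow-up rates and uses the estimated effect and the variability of the outcomes to design the definitive trial. The economic analysis compares resource use with usual care alone. Usual-care retention and resource use come from the control arm, and a reader would take them to rest on 30 families.

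**Working it through.** **Inputs from the protocol article.** Total 60 families and 30 per group (Sample size); 1:1 (Randomisation); 2:1 added later, start point not stated (Table 4).

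**Assumptions.** The total stays at 60. A follow-up or uptake rate of 80% is used for illustration only, because the article gives no expected rate.

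**Step 1: reproduce the stated figure.** 60 × 1/2 = 30 per group. It matches under 1:1.

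**Step 2: expected controls when the first m families are allocated 1:1 and the rest 2:1.** Controls = m/2 + (60 − m)/3.

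- m = 0: 0 + 20 = 20 controls, 40 intervention
- m = 15: 7.5 + 15 = 22.5 controls, 37.5 intervention
- m = 30: 15 + 10 = 25 controls, 35 intervention
- m = 45: 22.5 + 5 = 27.5 controls, 32.5 intervention
- m = 60 (no 2:1 at all): 30 controls, 30 intervention

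Any use of 2:1 puts the expected control arm below 30. Keeping 30 controls with 2:1 throughout would take 30 × 3 = 90 families.

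**Step 3: precision of the arm difference.** The standard error in SD units is √(1/n₁ + 1/n₂). The equivalent 1:1 total is 4n₁n₂/(n₁ + n₂).

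- 30:30: √(1/30 + 1/30) = 0.258; equivalent total 60
- 35:25: √(1/35 + 1/25) = 0.262, ratio 1.014; equivalent total 58.3
- 40:20: √(1/40 + 1/20) = 0.274, ratio 1.061; equivalent total 4 × 40 × 20/60 = 53.3

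The t-based 95% half-width goes from 0.517 SD at 30:30 to 0.548 SD at 40:20.

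**Step 4: precision of a rate within one arm.** Half-width = 1.96 × √(0.8 × 0.2/n).

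- n = 20: 17.5 points
- n = 25: 15.7 points
- n = 30: 14.3 points
- n = 35: 13.3 points
- n = 40: 12.4 points
- all 60 families together: 10.1 points, whatever the split

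At the 40:20 bound, a control-arm rate therefore loses about 3 points of half-width and an intervention-arm rate gains about 2.

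**The case against.** The change is disclosed, approved and explained, and Table 4 judges it suitable for a feasibility trial. The main text can be read as the design at the outset, for which 30 per group is correct arithmetic. That answers any charge of concealment. It does not repair the justification: Table 4 records the rule now in force rather than superseded text, and it says nothing about arm sizes.

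The effect is small, and this stands. No power claim is made. The 40:20 split is the extreme case, and even there the standard error of the contrast rises only 6%. Uptake and adherence, which are among the primary objectives, are measured in the intervention arm and are estimated more precisely under 2:1. The planned regression pools residual variance over both arms, so the control-arm SD alone is not the quantity the plan relies on.

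The source of the pilot-study recommendation is not at hand, so it cannot be said that 20 to 29 controls falls outside it. Only the stated figure of 30 is known not to fit.

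A reader might also infer that the enlarged intervention arm would overfill the groups. The article says "We aim to run a minimum of three sets of child and adolescent groups and three parallel parent groups over the three recruitment sites" and "Young SMILES is an 8-week group programme (4–6 CYP per group) split into two age bands, namely 6–11 and 12–16". If each set is one group per age band, that is 3 × 2 × 4 = 24 to 3 × 2 × 6 = 36 places, against 40 children from 40 families at one child each. The documents do not support this inference, for four reasons:

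- Three sets is a floor. The Forecast execution dates section foresees further groups starting until the end of June 2018, and no maximum is given.
- The Recruitment section makes baseline interviews wait for enough referrals in one age band at one site, so groups are formed around the families available.
- The overflow needs 2:1 for all 60 families and uptake above 36/40 = 90%, or an assumed number of children per family.
- The pressure is not specific to 2:1. At 1:1, more than 36/30 = 1.2 children per family would already exceed 36 places.

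**Conclusion.** The point holds in a limited form. The only stated reason for 60 families is a per-group size that the approved allocation cannot be expected to deliver for controls. If the total stays at 60, the expected control arm is 20 with 2:1 throughout, about 25 if half the families were randomised 1:1, and below 30 in every case where 2:1 is used at all.

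The cost is modest for the treatment contrast and larger for control-arm rates, with a partial gain on the intervention side. The size within that range depends on when 2:1 began, which the article does not state, and the half-widths for rates depend on the assumed 80%.

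The documents do not show that 2:1 is unsuitable, that the trial cannot meet its feasibility aims, or that families would be left without a group place.

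**What to change.** In the Sample size section:

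- State from which family 2:1 applies and whether the total remains 60.
- Replace 30 per group with the expected arm sizes under the allocation used: between 20 and 30 controls and between 30 and 40 intervention families if the total stays at 60, narrowed to one pair of numbers once the start point is given.
- Base the adequacy statement on the precision those sizes give for follow-up, uptake and the arm difference, instead of on the 30-per-group recommendation.
- Bring the 1:1 statements in the abstract and the Randomisation section into line with Table 4, or refer to it there.

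This changes text only and leaves recruitment, allocation and analysis as they are. The cost is a less favourable stated precision for the control arm, offset by a better one for the intervention arm. No change to the number of groups or to the reporting of uptake follows from this point.
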